## Abstract

**Background:**

The reduction of goal-directed behavior is the main characteristic in motivational negative symptoms of psychosis as it accounts for the long-term decline in psychological well-being and psychosocial functioning. However, the available treatment options are largely unspecific and show only small effects on motivational negative symptoms. Interventions that directly target the relevant psychological mechanisms are likely to be more effective. For “Goals in Focus”, we translated findings from basic clinical research on mechanisms underlying motivational negative symptoms into a tailored and comprehensive novel psychological outpatient treatment program. With this study, we will test the feasibility of the therapy manual and the trial procedures. We also aim to examine first estimates of the effect size that can be expected from “Goals in Focus” to inform the sample size calculation of a subsequent fully powered trial.

**Methods:**

Thirty participants diagnosed with a schizophrenia spectrum disorder and at least moderate motivational negative symptoms will be randomly assigned to either 24 sessions of “Goals in Focus” over the course of 6 months (*n* = 15) or to a 6-month wait-list control group (*n* = 15). Single-blind assessments will be conducted at baseline (*t*_0_) and 6 months after baseline completion (*t*_1_). Feasibility outcomes include patient recruitment, retention, and attendance rates. Acceptability will be rated by trial therapists and by participants at end of treatment. Primary outcome for effect size estimation is the motivational negative symptom subscale sum score of the Brief Negative Symptom Scale at *t*_1_ corrected for baseline values. Secondary outcomes include psychosocial functioning, psychological well-being, depressive symptoms, expressive negative symptoms, negative symptom factor scores, and goal pursuit in everyday life.

**Discussion:**

The feasibility and acceptability data will be used to improve trial procedures and the “Goals in Focus” intervention where necessary. The treatment effect on the primary outcome will provide the basis for the sample size calculation for a fully powered RCT.

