#### Recruitment, randomization, and blinding

Participants are recruited from outpatient settings in Hamburg (i.e., clinical psychologists and psychiatrists in private practice, social services), psychiatric clinics, and local self-help groups. Participants are either referred to the study by practitioners or via self-referral.

Enrolled and potentially eligible participants are invited for a study information meeting with a trial therapist. The participant will receive a copy of the participant information sheet which provides detailed information about the aims of the study and trial procedures. Participants are given the opportunity to ask questions. Following the information meeting, participants have sufficient time (24 h to 1 week) to consider their participation. After providing informed consent, participants meet with a trial rater who assesses eligibility and completes the baseline assessment with eligible participants. Clinical interviews are conducted by trial raters (psychologists in clinical training with at least master’s degree). All raters have already undergone training in basic therapeutic skills, such as assessment and building rapport. All raters receive a 4-h rater training by the trial manager on all of the observer-rated measures used in this trial. Allocation to either treatment- or wait-list control group is conducted (1:1) using permuted blocks of 4, 6, and 10 to reduce predictability of the sequence. The randomization schedule is generated and preserved by an assistant of the work group who is not otherwise involved in trial procedures. The trial manager is informed about the participant’s group allocation and notifies the participant and the responsible trial therapist.

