#### Sample size

An a priori power calculation is not appropriate for this feasibility trial as the study aim is not to test efficacy. Nonetheless, we aim to examine first effect size estimates of “Goals in Focus” on our primary and secondary outcomes. These estimates will inform the sample size calculation for a future fully powered RCT. Based on the recommendations for feasibility studies [75] and on existing feasibility trials in this field [76, 77], the target for this feasibility study was set at *N* = 30 participants (*n* = 15 intervention group; *n* = 15 wait-list control group).

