#### Analysis plan

Feasibility and acceptability will be analyzed by calculating descriptive statistics based on the intention-to-treat (ITT) population. Potential reasons for trial withdrawal will be examined by comparing baseline characteristics (e.g., symptom severity, sociodemographic variables, etc.) between participants who completed the trial and participants who discontinued their participation after randomization.

Clinical outcomes at baseline assessment (*t*_0_) and 6-month assessment (*t*_1_) will be summarized using descriptive statistics (i.e., frequency and percentages on binary and categorical variables; means, standard deviations, or medians, with minimum and maximum values for continuous variables) for each arm of the trial separately. Wait-list control and treatment group characteristics at baseline will be compared using Pearson chi-square tests for the categorical variables and the *t*-test or Mann–Whitney test for the quantitative variables.

Confirmatory analysis will be conducted for primary and secondary outcomes based on the ITT population. An ANCOVA adjusted for baseline values will be calculated with group allocation as between-subject factor and time as within-subject factor. Any variables that show significant group differences at baseline or are found to correlate with the primary outcome (e.g., age, gender, diagnosis, medication doses, duration of illness, symptom severity, etc.) will be entered as covariates. Effect sizes between and within treatment conditions will be assessed by calculating Cohen’s *d*. Missing values will be handled by multiple imputation, if missing completely at random [93]. All analyses will be carried out using validated statistical software.

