“Goals in Focus” was developed to directly target the relevant motivational negative symptom domains by translating recent empirical research on factors and mechanisms underlying motivational negative symptoms into specified interventions. The comprehensive treatment approach is tested in a randomized controlled trial design which allows to eliminate a possible selection bias and to control for spontaneous remission effects. However, there are some limitations to our study design: this is a pilot trial with the main focus on feasibility and the sample of 30 participants is not sufficient for a reliable efficacy analysis. As likelihood of type 1 error inflation is high, results of significance tests cannot be interpreted, but effect sizes derived from the present study will be used for a priori sample size calculation for a subsequent fully powered RCT. The advantage of a wait-list control condition is that it allows a first estimation of effects and enables wait-list participants to later receive the same intervention. Also, diffusion effects between the conditions (e.g., patients from the wait-list group receiving information about the intervention from other patients, therapists including intervention elements in standard treatment) are unlikely due to the outpatient setting and the fact that treatment as usual is not provided by trial therapists. A disadvantage is that the wait-list comparator may artificially inflate estimates of the intervention effect, due to participants being held in a waiting position and less likely to initiate behavioral change on their own (e.g., as suggested by Cunningham et al. [94]). Additionally, the eligibility criterium of “being able to engage in weekly therapy sessions of 50 min” limits the generalization of effects to those who are not able to attend weekly sessions for the full-time range of 50 min. Other issues that warrant mention relate to the selected outcomes: since “Goals in Focus” aims at improving goal setting and achievement, the EMA of goal pursuit is of particular interest. However, participants’ adherence to an autonomously conducted 1-week survey might be reduced, which is why we did not select it as the primary outcome. Also, a long-term follow-up was not included at this point due to the primary focus being on acceptability, feasibility, and first estimates of efficacy. It also needs to be kept in mind, that the intervention only targets motivational negative symptoms and not expressive negative symptoms, the other relevant component of negative symptoms [72, 95]. However, we expect expressive negative symptoms to be indirectly affected by the intervention as suggested by results reported by Choi et al. [18] in relation to a similar treatment approach. Accordingly, expressive negative symptoms are evaluated as a secondary outcome. Similarly, the intervention does not target contextual factors, such as social deprivation or health-related issues that are likely to exacerbate negative symptoms, but expect the achievement of personal goals due to the intervention to partially improve participants’ challenging contextual factors as well.

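### The full RCT is to be sized on the treatment effect observed in 30 pilot participants, an estimate too imprecise for that use and, by the protocol's own account, possibly inflated

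*Protocol article*

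**What the plan says.** The article describes the use of the pilot effect with differing strength. The Discussion paragraph of the Abstract is the firmest: "The treatment effect on the primary outcome will provide the basis for the sample size calculation for a fully powered RCT". The Discussion section also says that effect sizes from this study will be used in the later trial's a priori calculation. The Background paragraph of the Abstract, the end of the Background section and the Sample size section say only that the estimates will inform it.

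The Discussion section states two limits on the same estimate: "the sample of 30 participants is not sufficient for a reliable efficacy analysis", and "the wait-list comparator may artificially inflate estimates of the intervention effect". It adds that significance tests cannot be interpreted.

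The pilot's own size does not come from a precision or power argument. The Sample size section says "An a priori power calculation is not appropriate for this feasibility trial as the study aim is not to test efficacy" and sets 15 per arm from feasibility recommendations and precedent.

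**The concern.** An effect estimate and a significance test from the same 30 people carry the same sampling error. The Discussion sets the test aside as uninterpretable and, in the same sentence, keeps the effect size as the planning input. The required sample size varies with the inverse square of the effect, so moderate error in d becomes large error in N.

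The two directions of error have different consequences. If the pilot overestimates the effect, the RCT is too small and may fail to detect a real benefit. If it underestimates, the RCT is too large or is not run. The bias that the protocol itself names, from the wait-list comparator, acts in the first direction. Informing the size of the full RCT is a declared aim of the pilot, so this is worth putting right before that calculation is made.

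**Working it through.** The plan gives no alpha, power, SD or effect size for either trial, so there is no figure of its own to reproduce. The check asks how precise the pilot effect can be and what follows if an RCT is sized on it.

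**Inputs from the protocol.** 30 participants, 15 per arm (Abstract, Sample size); 1:1 allocation (Recruitment, randomization, and blinding); baseline-adjusted analysis and Cohen's d (Analysis plan).

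**Assumptions.** Two-sided alpha 0.05 and 80% power for the RCT; true d = 0.4 (the Background calls the effects of existing treatments small to moderate, without a figure); correlation r between baseline and 6-month scores from 0 to 0.7; all 30 analysed.

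**1. Precision, unadjusted.** SE(d) = sqrt(2/15 + d²/60). At d = 0.5 this is sqrt(0.1333 + 0.0042) = 0.371. The 95% interval is 0.5 ± 1.96 × 0.371 = -0.23 to 1.23, width 1.45. Noncentral-t inversion agrees to within 0.01. With 12 or 13 analysed per arm, the width is 1.54 to 1.70 for d between 0 and 1.

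**2. Precision, baseline-adjusted.** Width in SD units = 2 × t(0.975; 27) × sqrt((1 - r²) × 2/15), with t = 2.052.
- r = 0.3: 4.104 × 0.348 = 1.43
- r = 0.5: 4.104 × 0.316 = 1.30
- r = 0.7: 4.104 × 0.261 = 1.07

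**3. What this does to N.** n per arm = 2 × (2.8016/d)², rounded up: 393 at d = 0.2, 99 at 0.4, 63 at 0.5, 25 at 0.8 and 11 at 1.2. The interval around an observed 0.5 therefore runs from no finite N to about 11 per arm.

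**4. How often the RCT would be underpowered.** Percentages are shares of all pilots.
- *Pilot d zero or negative.* The adjusted SE of the difference is 0.365 × sqrt(1 - r²). At r = 0, 0.4/0.365 = 1.10, giving 14%. At r = 0.7, 0.4/0.261 = 1.53, giving 6%.
- *RCT analysed unadjusted.* Power is below 80% whenever the pilot d exceeds 0.4, in about 50% of pilots. It is below 50% when the pilot d exceeds 0.4 × 2.8016/1.96 = 0.572. SE(d) at 0.4 is sqrt(0.1333 × (1 - r²) + 0.0027): 0.369 at r = 0 and 0.266 at r = 0.7. So z = 0.172/0.369 = 0.47 (32%) and 0.172/0.266 = 0.65 (26%).
- *RCT also baseline-adjusted, r = 0.7, but sized on the raw-SD d.* Both thresholds are divided by sqrt(1 - 0.49) = 0.714, giving 0.560 and 0.801. So z = 0.160/0.266 = 0.60 (about 28% of pilots below 80% power) and 0.401/0.266 = 1.51 (about 7% below 50%).

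Simulation of the same steps gives the same percentages to within about one point. None of them includes wait-list inflation.

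**The case against.** The strongest reply is that this is a feasibility trial. Its main outputs are recruitment, retention, attendance and acceptability, and 15 per arm is a reasonable size for those. The authors disclose both limitations, three of the five places say only that the estimates will inform the later calculation, and the later trial will have its own protocol. All of that stands. It limits the point to the stated use of the estimate and leaves the pilot's own validity untouched.

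Four stronger readings are tempting and are not supported.
- *The protocol calls its estimate inflated.* It says only that the comparator may inflate it.
- *The raw point estimate will be used with no interval or correction.* The article does not say so. It is a condensed account, and the absence of an interval or lower bound in it is no finding. What can be criticised is the wording that makes the effect the basis of the calculation.
- *Within-arm effect sizes, open to regression to the mean, will size the RCT.* The Analysis plan says "Effect sizes between and within treatment conditions will be assessed by calculating" Cohen's d, but this is a list of reported statistics. The Abstract ties the RCT's size to the treatment effect on the primary outcome, which is the baseline-adjusted 6-month score compared between randomised arms. Regression to the mean affects both arms and does not bias that comparison.
- *A quarter to a third of RCTs would have under 50% power whatever the analysis.* That holds only if the RCT is unadjusted. Crediting the pilot with baseline adjustment and denying it to the RCT overstates the risk at high r.

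**Conclusion.** The point holds in limited form. The Abstract and Discussion tie the RCT's size to an effect estimate that cannot separate a small effect from a large one: the 95% interval is about 1.45 wide unadjusted and 1.1 to 1.4 SD adjusted. The Discussion itself gives reasons for caution about that estimate. With a true d of 0.4, an RCT sized this way has under 80% power after about 28% to 50% of pilots, and under 50% power after about 7% to 32%. The lower ends apply if both trials gain from baseline adjustment at r = 0.7, and the upper ends if neither does. The width of the unadjusted interval depends only on the planned numbers and the observed d. The power figures are illustrations that depend on the assumed d, r, alpha and power. Any wait-list inflation would come on top and would shrink the RCT further. Nothing in the pilot's conduct, size or feasibility analysis needs to change.

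**What to change.** Reword the Discussion paragraph of the Abstract and the matching sentence in the Discussion section. Bring the Background paragraph of the Abstract, the end of the Background section and the Sample size section into line. State that:

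- the pilot supplies the SD of the BNSS motivation-and-pleasure score at 6 months, the correlation between baseline and 6-month scores, and retention;
- the RCT's target difference is set from a clinically relevant BNSS difference;
- the pilot's baseline-adjusted between-arm difference is reported with its 95% confidence interval and used only to check that the target is not excluded.

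The cost is wording only: no new data, participants or procedures. The drawback is that the planned RCT may turn out larger than one sized on a favourable pilot effect.

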**Trial registration:**

1) ClinicalTrials.gov, NCT05252039. Registered on 23 February 2022.

2) Deutsches Register Klinischer Studien, DRKS00018083. Registered on 28 August 2019.

**Supplementary Information:**

The online version contains supplementary material available at 10.1186/s40814-023-01284-4.

## Background

Apathy, anhedonia, and social withdrawal constitute the motivational factor of negative symptoms [1, 2] and are evident in approximately 60% of people with psychotic disorders [3]. Compared to positive symptoms and the expressivity factor of negative symptoms (i.e., alogia and blunted affect), motivational negative symptoms account for the reduced levels of long-term functioning [4, 5] and the low quality of life [6, 7]. Consequently, both clinicians [8] and patients [9] consider motivational negative symptoms an important treatment target.

Several meta-analyses found that psychological approaches, such as cognitive behavior therapy (CBT), social skills training, and cognitive remediation, can alleviate motivational negative symptoms, however, with only small to moderate effect sizes [10-14]. Reasons for these rather unsatisfying effect sizes could be that the available interventions were either not derived from empirical knowledge about negative symptoms and that each intervention targets only single factors, e.g., social skills [15], beliefs [16], or goal pursuit [17, 18]. Also, emerging qualitative research has emphasized the importance of user involvement in the development of interventions for psychosis [19, 20]. Meanwhile, empirical research on psychological mechanisms of motivational negative symptoms has gained momentum. This has considerably refined and extended our understanding of the factors that are likely to be relevant to the formation and maintenance of negative symptoms. This research now provides a comprehensive set of factors that can be, and in our view *should* be, addressed by psychological interventions. As we will outline in the following, these include goal setting, altered reward processing, anticipatory anhedonia, demotivating beliefs as well as reduced social and problem-solving skills (for an overview see [21]).

Goal setting. Even though people with negative symptoms set personal life goals [22], they report difficulties initiating and maintaining behavior towards goal realization [23]. More fine-grained analyses of short-term goals in a subclinical sample in daily life indicate an association between negative symptoms and setting too many avoidance goals [24]. This is likely to explain the reduced approach-oriented [25] and increased avoidance-oriented behavior [26]. In addition to these internal challenges, several external challenges, such as social deprivation [27] and stigmatization [28, 29], may render it more difficult to set approach-focused goals in this population [30]. Thus, effective psychosocial interventions aimed at optimizing goal pursuit ideally need to address both internal and external challenges. This could be done by encouraging the setting of personally meaningful, specific, measurable, attractive, realistic, and time-bound approach goals that are also suited to optimize the individuals’ external social situation.

Altered reward processing. People with motivational negative symptoms have also been found to display problems in reinforcement learning [26, 31, 32], prediction of reward cues, generating, updating, and maintaining value representations [33-36], exploratory behaviors with uncertain reward-outcomes [37], and unfavorable trade-offs in effort-value computations [5, 33, 34, 38]. Intervention targets that can be derived from this research on reward processing include training the mental representation of a reward and developing an accurate estimation of the effort necessary to achieve a goal.

Anticipatory anhedonia. Recent reviews point towards a reduced ability to anticipate pleasure for future events in people with negative symptoms [39, 40], despite intact ability to experience in-the-moment pleasure [41]. This problem in anticipatory pleasure has been found to mediate the translation of goal intentions into goal-directed behavior [42]. Research from basic neuroscience has found that the anticipation of positive future events draws strongly on the ability to recall pleasant episodic memories [43]. However, this ability has also been found to be reduced in people with negative symptoms [44, 45]. Taken together, this research indicates that improving anticipatory anhedonia could be a key to improve motivation. This could be achieved by supporting the recall of episodic memories about similar past pleasurable experiences [46] and by building on the intact ability to experience consummatory pleasure [47, 48].

Demotivating beliefs. Demotivating beliefs about self (self-defeating beliefs), others (social indifference beliefs), and the future (low expectancy of pleasure) (see [49-52]) have been found to account for one third of variance in amotivation [44, 52] and to impede the willingness to exert effort [53]. Particular attention has been given to a specific aspect of self-defeating beliefs, namely, defeatist performance beliefs (e.g., “If you cannot do something well, there is little point in doing it at all.”) that are associated with a reduced level of functioning [54]. It follows that identifying, challenging, and gradually modifying these specific beliefs could be another promising treatment approach.

Reduced interpersonal and problem-solving skills. Impaired social skills and social cognition have long been associated with motivational negative symptoms [55, 56]. Targeting social skills has been shown to improve negative symptoms [57-59]. Similarly, difficulties in the ability to solve problems in an effective and timely manner have been repeatedly found to be associated with psychosis in general [60] and negative symptoms specifically [61]. Training of problem-solving skills has also become a well-established approach in the treatment of psychosis [62, 63]. Accordingly, effective interventions for people with negative symptoms would be advised to include a focus on problem-solving skills and to encourage the translation of these skills into daily life.

We argue that each of these factors contributes to the observed difficulties of patients with negative symptoms in pursuing personally meaningful goals. It follows that interventions that specifically target these factors are likely to be more successful in reducing motivational negative symptoms than less specific interventions, such as behavioral activation and cognitive therapy. Given that each of these factors is associated with negative symptoms but none of them can fully account for negative symptoms, we also expect approaches addressing several of these factors to be superior to interventions that focus on a single factor. This expectation is corroborated by the fact that approaches that have targeted several of these factors, e.g., by combining cognitive interventions with social skills training [64] or with interventions targeting anhedonia [65-67], tend to produce more promising effects. In addition, given that the factors driving amotivation might vary between patients, we argue that intervention approaches will more likely be effective if their focus can be flexibly adjusted to the individual needs of a given patient [21]. However, to our knowledge, there is no approach that addresses the full range of relevant mechanisms in a customizable manner.

On that account, we developed a novel comprehensive, individualized cognitive behavioral outpatient intervention (“Goals in Focus”) that supports patients in specifying attainable personal goals and overcoming obstacles in goal pursuit. The intervention aims at supporting patients to realize personally meaningful goals by addressing reward processing, anticipatory pleasure, demotivating beliefs, and social and problem-solving skills.

With this feasibility trial, we aim to test the feasibility (i.e., referrals, eligibility rate, number of consenting participants, retention rate, attendance rate, dose of intervention, data attrition, and treatment adherence) and acceptability (i.e., drop-out rate, number of adverse events, participants’ and therapists’ satisfaction) of the therapy manual and trial procedures as well as to obtain first estimates of the effect size that can be expected from “Goals in Focus” (i.e., extent of change in motivational negative symptoms as primary outcome) to inform the sample size calculation for a fully powered clinical trial.

